#### Analysis Population, Missing Data, and Sensitivity Analyses

The primary analysis will follow the intention-to-treat principle, in which all participants will be analyzed in the groups to which their hospital was allocated, regardless of their level of app use, exposure to the leaflets, or subsequent adherence. Every effort will be made to obtain outcome data at 1 and 3 months for all enrolled caregivers, including those who discontinue or reduce use of the intervention [49].

Missing outcome data will initially be handled within the GEE framework, which uses all available repeated measurements under a missing-at-random assumption and provides robust standard errors. Patterns and reasons for missing data will be described. If more than a small proportion of outcome data (>20%) is missing, multiple imputation by chained equations will be considered as a sensitivity analysis, with covariates and outcome scores imputed under the missing-at-random assumption. Results from imputed and complete-case analyses will be compared to assess the robustness of the findings [21].

This study was conducted without any specific external financial support or grants from any public, commercial, or not-for-profit funding agencies. Recruitment and baseline data collection are currently underway at the time of manuscript submission (phase 1: 210 participants, phase 2 not yet started at the time of submission). The study findings are expected to be published in December 2026.

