### Sample Size Calculation

The sample size for Phase 2 was calculated for comparison of 2 independent means (intervention vs control) assuming equal group sizes, a 2-sided test with a significance level of *α*=.05, and power (1−β)=0.80. The calculation followed the method described by Rosner [43] and Turnbull et al [44]. The required sample size per group was obtained using the formula:

$$n=\frac{(\sigma_{1}^{2}+\sigma_{2}^{2})(Z_{1-\alpha /2}+Z_{1-\beta }{)}^{2}}{\Delta^{2}}$$

where $\sigma_{1}$ and $\sigma_{2}$ are the SDs in the 2 groups, $Z_{1-\alpha /2}$ is the standard normal deviate at the 5% (1.96) significance level, $Z_{1-\beta }$ is the standard normal deviate for 80% (0.84) power, and Δ is the expected mean difference between the groups.

Based on Turnbull et al [44], an expected mean difference in knowledge scores of 1.69 was used, with SDs of 2.53 and 2.76, respectively. Substituting these values:

$$n=\frac{(2.53^{2}+2.76^{2})(1.96+0.842{)}^{2}}{1.69^{2}}\approx 38.5$$

Thus, approximately 39 participants are required per group. To account for an anticipated 30% attrition rate, the sample size was inflated:

$$n_{\text{adjusted}}=38.5\times 1.30\approx 50$$

Accordingly, 50 participants will be recruited into each arm (intervention and control), giving a total sample size of 100 caregivers.

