#### Inferential and Longitudinal Analysis

All analyses will be conducted using a 2-sided significance level of *α*=.05. Descriptive statistics will summarize sociodemographic and caregiving characteristics by study arm [46]. Categorical variables will be presented as frequencies and percentages, and continuous variables as means and SDs or medians and IQRs, as appropriate. Baseline comparability between the intervention and control groups will be examined using chi-square tests for categorical variables and independent *t* tests (or nonparametric equivalents) for continuous variables [46,47].

The primary effectiveness analysis will use generalized estimating equations models to compare changes in knowledge, attitude, practice, and burden scores between the intervention and control groups over time (baseline, 1 mo, and 3 mo). For each outcome, a GEE model with an appropriate link function and working correlation structure will be fitted, including fixed effects for group (intervention vs control), time, and the group-by-time interaction. The group-by-time interaction term will be interpreted as the main estimate of the intervention effect. To account for potential confounding due to nonrandom allocation, the models will adjust for prespecified baseline covariates (age, sex, and relationship with the people living with dementia, caregiving duration, and baseline score of the corresponding outcome). Robust standard errors will be reported [21,48].

Effect sizes (Cohen *d* for between-group differences in mean change) will be calculated to quantify the magnitude of the intervention effect, in addition to *P* values and 95% CIs [21,48].

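### The plan says its primary GEE covers outcomes missing at random; unweighted available-case GEE generally does not, so the month-3 estimate can be biased in either direction

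*Protocol article*

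**What the plan says.** In the Protocol article, Analysis Population, Missing Data, and Sensitivity Analyses, the missing-data rule for the primary analysis is: "Missing outcome data will initially be handled within the GEE framework, which uses all available repeated measurements under a missing-at-random assumption". The same sentence adds that robust standard errors are provided. Imputation comes next, conditionally: "If more than a small proportion of outcome data (>20%) is missing, multiple imputation by chained equations will be considered as a sensitivity analysis". Imputed and complete-case results would then be compared.

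The model is described under Inferential and Longitudinal Analysis: "The primary effectiveness analysis will use generalized estimating equations models to compare changes in knowledge, attitude, practice, and burden scores". Its structure is left partly open: "a GEE model with an appropriate link function and working correlation structure will be fitted". The section also says that "the models will adjust for prespecified baseline covariates", and the list includes the baseline score of the outcome being analysed. On the estimate: "The group-by-time interaction term will be interpreted as the main estimate of the intervention effect".

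Under Sample Size Calculation, the target is inflated for "an anticipated 30% attrition rate".

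**The concern.** Missing at random (MAR) allows dropout to depend on anything already observed, including a participant's own earlier scores. Unweighted GEE on the available records does not generally give a consistent estimate under that condition. It does so when missingness is completely at random (MCAR), or when it depends only on covariates in a mean model that is correctly specified. It does so approximately when both the mean and the working correlation are correct with an identity link, because the estimate is then close to a Gaussian likelihood fit. Robust standard errors repair the variance, not a shifted mean.

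The article therefore credits its primary method with a property that the method, as described, does not generally have. The conditions that could rescue it are not secured:

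- **Working correlation.** It is not fixed.
- **Baseline score.** Baseline is listed among the analysed time points and is also a covariate. One common slope for it across three visits can misspecify the mean.
- **Dropout relation.** The arms receive different materials, and only the app arm gets scheduled reminders to keep using an app (Engagement and Adherence Monitoring). An identical dropout relation in both arms cannot be taken for granted.

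At stake is the month-3 group-by-time estimate, in a comparison that is already nonrandomized.

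**Working it through.** **1. The plan's own figures.** Inputs from Sample Size Calculation: difference 1.69, SDs 2.53 and 2.76, multipliers 1.96 and 0.842, attrition 30%.

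- n = (2.53² + 2.76²)(1.96 + 0.842)² / 1.69² = 14.0185 × 7.8512 / 2.8561 = 38.54 per arm. This matches the article's 38.5.
- 38.54 × 1.30 = 50.1, matching the article's 50 per arm.

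The 30% attrition figure is thus the plan's own.

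**2. Yardstick.** Common SD = √(14.0185/2) = 2.65. With 50 × 0.70 = 35 completers per arm, the standard error of a simple difference is 2.65 × √(2/35) = 0.63.

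**3. Simulated bias of the month-3 effect.** The documents give no correlations and no dropout mechanism, so these are assumptions.

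- True effect 1.69, SD 2.65, about 30% dropout at month 3.
- Unweighted Gaussian GEE with identity link; four runs of 10,000 subjects per cell; Monte Carlo error about 0.03 to 0.05.
- True correlation: exchangeable 0.6, or AR(1) 0.7.
- Score-dependent dropout: log-odds change of 1.5 per SD of the observed score.
- Model B: all three visits as responses plus baseline score as covariate. Model C: months 1 and 3 as responses, baseline score as covariate.
- Each cell gives bias for true correlation exchangeable 0.6 / AR(1) 0.7.

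| Dropout at month 3 | B, independence | B, exchangeable | C, independence | C, exchangeable |
|---|---|---|---|---|
| Completely at random | 0.00 / −0.01 | +0.02 / +0.02 | +0.02 / 0.00 | +0.01 / −0.02 |
| Low month-1 scorers leave, both arms alike | +0.01 / +0.01 | +0.04 / −0.01 | −0.01 / +0.01 | −0.05 / −0.04 |
| Low month-1 scorers leave the app arm; control random | +0.13 / +0.18 | +0.10 / +0.05 | +0.21 / +0.26 | 0.00 / −0.05 |
| Low month-1 scorers leave the app arm, high ones leave control | +0.25 / +0.28 | +0.14 / +0.10 | +0.43 / +0.52 | +0.04 / −0.02 |
| Low baseline scorers leave the app arm, high ones leave control | −0.26 / −0.49 | −0.34 / −0.60 | +0.02 / −0.21 | −0.05 / −0.32 |

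Two further simulations, also on assumed settings:

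- Milder dropout (log-odds 1 per SD, app arm only, control random) with model B: +0.03 to +0.11 for month-1-dependent dropout, and −0.23 to −0.11 for baseline-dependent dropout.
- A separate check with the baseline covariate and arm-differential dropout: −0.27 to +0.28.

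In relative terms, 0.28/1.69 = 17% of the effect and 0.28/0.63 = 0.44 standard errors. At the extremes, 0.52/1.69 = 31% and 0.60/1.69 = 36%.

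**4. Does 30% attrition meet the 20% condition?** Take 100 participants and three visits, so 300 measurements, of which 200 are post-baseline.

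| 30 participants miss | Share of all measurements | Share of post-baseline | Share of month-3 |
|---|---|---|---|
| Month 3 only | 30/300 = 10% | 30/200 = 15% | 30% |
| Months 1 and 3 | 60/300 = 20% (not above 20%) | 60/200 = 30% | 30% |

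The answer depends on a denominator that the article does not state.

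**The case against.** The strongest reply is that the damage is modest and conditional. The plan adjusts for the baseline score. With that adjustment and mild month-1-dependent dropout in the app arm alone, the bias is at most about 0.11, or 0.11/0.63 = 17% of a standard error. Exchangeable working correlation removes most of the bias from month-1-dependent dropout. The article commits to pursuing 1- and 3-month data even from those who stop using the intervention, and it does foresee imputation. The choice of working correlation is often left to an analysis plan, which is not shown. All of this stands, and it limits the size of the point. It does not make the missing-at-random statement correct, and exchangeable correlation does not protect against baseline-dependent dropout in the bottom row of the table.

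Three stronger readings are tempting, and the documents do not support them:

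- **That GEE strictly needs MCAR.** It does not; the exceptions are given above.
- **That the app's benefit will be inflated, by 18 to 25%.** That size (+0.30 to +0.42 on 1.69) arises only with independence correlation and no baseline score in the model, whereas the article requires the baseline score. The direction is also open: no dropout mechanism is stated, and the simulated bias takes both signs.
- **That the 20% condition is already expected to be met.** The 30% refers to participants and the 20% to outcome data. On all measurements, 30% attrition gives 10% to 20% missing, which does not exceed the threshold.

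**Conclusion.** The point holds as an error in a stated property. The article says its primary GEE handles outcomes missing at random, and the unweighted available-case method it describes does not do so in general. The consequence is possible bias in either direction in the month-3 group-by-time estimate, if dropout depends on earlier scores differently by arm. With the baseline covariate, a reasonable working size is −0.3 to +0.3 points, or about half a standard error at most. Values near +0.5 (month-1-dependent dropout, independence correlation) and −0.6 (baseline-dependent dropout, baseline score as both response and covariate) need strong dropout in opposite directions in the two arms. If dropout relates to scores in the same way in both arms, or is completely at random, the bias is about zero. All these sizes rest on assumed correlations and mechanisms at about 30% month-3 dropout. The planned imputation does not settle the matter, because it is optional, secondary and tied to an undefined threshold.

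**What to change.** - Correct the sentence: unweighted available-case GEE assumes that missingness is completely at random or depends only on covariates in a correctly specified mean model.
- Commit in advance, whatever fraction is missing, to one primary analysis that is valid under missing at random: GEE on multiply imputed data (imputing from baseline and month-1 scores, arm and covariates), inverse-probability-weighted GEE, or a likelihood-based repeated-measures model. Any of the three would do; the choice should be fixed before data are seen.
- Delete the 20% condition.
- Keep unweighted available-case GEE as the sensitivity analysis.

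The cost is revised analysis text and slightly more analysis work in standard software, with no additional data. The article reports that analysis has not begun and that Phase 2 had not started at submission, so the change can be made without knowledge of outcomes.

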### Phase 2: Effectiveness of the *DemensiaKITA* mHealth App

#### Overview

In Phase 2, the research assesses the effectiveness of the *DemensiaKITA* mHealth app intervention among dementia caregivers in Selangor, Malaysia. This phase uses an NRCT with 2 parallel arms (intervention and control) and a 1:1 allocation ratio. The study includes 3 assessment points: baseline (T0), 1 month (T1), and 3 months (T2). The intervention period spans from August 2025 to February 2026. Participants will be blinded to group allocation (single-blinded). Hospital-level allocation is applied to minimize contamination (Figure 2). Eligibility criteria for Phase 2 are given in Textbox 2.

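### The imputed versus complete-case comparison cannot detect bias from dropout that depends on unobserved outcomes and differs between arms, so agreement between the two should not be read as robustness to it

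*Protocol article*

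**What the plan says.** All statements are in the Protocol article.

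- **Analysis Population, Missing Data, and Sensitivity Analyses.** Missing outcomes are first handled by a GEE on all available measurements, stated to hold under missing at random. If more than 20% of outcome data are missing, multiple imputation by chained equations is something to be considered, "with covariates and outcome scores imputed under the missing-at-random assumption". The check is then: "Results from imputed and complete-case analyses will be compared to assess the robustness of the findings". No criterion for agreement is given, and no listed analysis departs from missing at random. The section also promises to describe patterns and reasons for missing data, and to pursue outcome data from caregivers who reduce or stop use.
- **Sample Size Calculation.** "To account for an anticipated 30% attrition rate, the sample size was inflated", giving 50 per arm.
- **Engagement and Adherence Monitoring; Data Collection Method and Study Tool; Comparator (Control Arm).** The app arm gets an app, with reminders weekly in the first month and every 2 weeks thereafter. The control arm gets leaflets and a video. Reminders check on app use in the intervention group.

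**The concern.** A robustness check is informative about an assumption only if one of the analyses compared relaxes it. Here one side assumes missing at random and the other, complete cases, generally assumes something stronger. Agreement shows that relaxing the stronger assumption made little difference. It does not address what happens if missing at random itself fails.

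That failure is plausible in this trial. The materials and the contact schedule differ by arm, and the outcome questionnaires are self-administered. A caregiver who gains little from the app may stop using it and stop answering, for reasons that earlier scores do not capture. If so, the imputed and complete-case estimates shift together, and two similar figures could be reported as a robust effect. The Discussion expects the findings to guide national policy, so the reading given to that agreement matters.

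**Working it through.** **Inputs from the protocol**

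| Input | Value | Section |
|---|---|---|
| Design difference | "an expected mean difference in knowledge scores of 1.69 was used" | Sample Size Calculation |
| SDs | "with SDs of 2.53 and 2.76, respectively" | Sample Size Calculation |
| Power | "power (1−β)=0.80" | Sample Size Calculation |
| Test level | "All analyses will be conducted using a 2-sided significance level of" 0.05 | Inferential and Longitudinal Analysis |
| Allocation | "2 parallel arms (intervention and control) and a 1:1 allocation ratio" | Overview, Phase 2 |
| Attrition | 30% | Sample Size Calculation |

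**Step 1: reproduce the stated figure.** n = (2.53² + 2.76²)(1.96 + 0.842)² / 1.69² = 14.0185 × 7.8512 / 2.8561 = 38.5, that is 39 per arm. Inflated as the protocol does it: 38.5 × 1.30 = 50. Both match. The pooled SD is √(14.0185 / 2) = 2.65. The protocol states no figure for the missing-data comparison itself.

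**Step 2: simulate with a true effect of zero.** 50 per arm, SD 2.65, three visits, and monotone dropout of about 30% overall. Assumed, because the protocol gives no values: within-person correlation 0.5 or 0.7, and logistic dropout with slope 1 or 2 per SD of score. Complete-case analysis is ANCOVA. Imputation is by arm from the baseline and 1-month scores, under missing at random, with 20 imputations. There were 1,000 runs per scenario. False positives are significant results favouring the app, nominally 2.5%.

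Results at correlation 0.5 (bias and difference in points; CC = complete case, MI = imputation):

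| Dropout depends on | Arms (slope app/control; loss app/control) | CC bias | MI bias | Mean absolute difference | CC false positive | MI false positive | Both | MI repeats a false CC positive |
|---|---|---|---|---|---|---|---|---|
| Unseen score | 1/1; 29%/29% | −0.01 | −0.02 | 0.10 | 2.5% | 1.7% | 1.5% | 60% |
| Unseen score | 1/0; 29%/30% | 0.38 | 0.36 | 0.10 | 10.6% | 9.4% | 8.5% | 80% |
| Unseen score | 2/0; 28%/30% | 0.53 | 0.52 | 0.10 | 17.3% | 14.7% | 13.6% | 79% |
| Unseen score | 1/−1; 29%/29% | 0.77 | 0.72 | 0.09 | 30.7% | 24.9% | 24.0% | 78% |
| Unseen score | 2/2; 37%/19% | 0.36 | 0.36 | 0.12 | 11.4% | 10.6% | 9.0% | 79% |
| Previous observed score | 2/0; 28%/30% | 0.11 | −0.04 | 0.19 | 3.6% | 1.8% | 1.5% | 42% |
| Previous observed score | 2/−2; 28%/28% | 0.31 | 0.01 | 0.31 | 6.9% | 1.9% | 1.9% | 28% |

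**Step 3: ranges over both correlations.**
- Unseen score, differing by arm: CC bias 0.17 to 0.77 and MI bias 0.16 to 0.72. The CC range is 0.17 / 1.69 = 10% to 0.77 / 1.69 = 46% of the design difference. False positives are 6% to 31% (CC) and 4% to 25% (MI). MI repeats 62% to 80% of false CC positives.
- Unseen score, same mechanism and rate in both arms: bias about 0.
- Observed score, differing by arm: CC bias 0.11 to 0.31, MI bias −0.04 to 0.01, and MI repeats 21% to 55%.
- GEE with an exchangeable working correlation (400 runs per scenario), unseen score differing by arm: bias 0.25 to 0.70 in the scenarios run. The primary analysis offers no independent protection.

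Reversing the arms reverses the sign of the bias.

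**Step 4: what a delta shift covers.** Shifting imputed values by δ moves an arm mean by the fraction missing times δ. With 30% missing and δ = 0.5 SD, that is 0.30 × 0.5 × 2.65 = 0.40 points for the app arm alone, and 0.80 points if the control arm is shifted equally the other way. The slope-1 app-only bias needs 0.36 / 0.29 = 1.24 points (0.47 SD). The slope-2 bias needs 0.52 / 0.28 = 1.86 points (0.70 SD).

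**Step 5: the 20% trigger.** At the 3-month visit, 30% attrition exceeds it. Counted over all three visits with baseline complete, the same attrition leaves 30% / 3 = 10% missing if all losses follow the 1-month visit, and 60% / 3 = 20% if all precede it. Neither is above 20%.

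**The case against.** The strongest reply has four parts.

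1. *The article is condensed, and an analysis plan not shown may hold a departure from missing at random.* That may be so, and the mere absence of such an analysis would be no finding. The point survives because the article itself names one comparison and gives it the purpose of assessing robustness, which it cannot serve for this kind of dropout.
2. *The comparison is a legitimate, limited check.* This stands. When dropout follows earlier observed scores, imputation removes the bias (0.31 to 0.01) and the gap from the complete-case result can show it. A reader might infer that any outcome-related dropout escapes notice, or that agreement says nothing at all. Neither is right.
3. *The scenarios are constructed.* Also fair. The protocol gives no differential dropout rate or mechanism. With the same mechanism and rate in both arms there was no bias. Knowledge is scored as correct or incorrect, not as perceived benefit. A second simulation, in which dropout depended on the caregiver's own change in the app arm only, gave larger biases (0.21 to 0.50 SD for complete cases, 0.15 to 0.38 SD for imputation). It let log-odds run to 3 per SD, an odds ratio of about 20, and used unadjusted change, so I do not rely on its size.
4. *The text contains mitigation.* Reminders also encourage follow-up, and reasons for missing data will be described. Both help and neither tests the assumption.

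**Conclusion.** The concern holds in a limited form. The stated comparison can reveal dropout that depends on earlier observed scores. It cannot detect bias from dropout that depends on unobserved follow-up outcomes and differs between arms. Under the assumed mechanisms, the two estimates then differed by only about 0.1 point on average while both were wrong by about 0.2 to 0.8 points.

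A reader might go further and infer that the plan would usually certify a false app effect as robust. The documents do not support that:
- Imputation is only to be considered, and no criterion for robustness is set, so there is no certifying rule.
- The 62% to 80% repetition is conditional on a false complete-case positive having arisen. Both analyses were falsely positive together in about 4% to 24% of runs in those scenarios.
- The bias need not favour the app.

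The sizes rest on the assumed correlations and dropout slopes. The structural point does not. What is affected is how far a finding may be called robust, not whether the trial can be run.

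**What to change.** In Analysis Population, Missing Data, and Sensitivity Analyses:

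1. Keep the imputed versus complete-case comparison, but describe it as a check on the stronger complete-case assumption only.
2. When the trigger of more than 20% missing is met, carry out the imputation by arm instead of only considering it. State that the percentage refers to the 3-month visit, so that the anticipated 30% attrition does trigger it.
3. Add a prespecified delta-adjusted analysis that shifts imputed 3-month outcomes separately by arm over a stated range, for example 0 to 0.5 SD in the direction unfavourable to the app. For the practice and burden scales, where higher is worse, that direction is upward in the app arm. Say what the range covers: 0.5 SD in the app arm alone offsets about 0.40 points at 30% missing, so a wider range or an opposite shift in the control arm is needed to cover the larger biases shown above.
4. Report the delta at which the 3-month effect loses significance, next to the reasons for missing data.
5. If an analysis plan already contains such an analysis, cite it here.

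Control-based imputation is not needed. It would borrow trajectories from different, non-randomly allocated hospitals.

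Cost: wording and a few lines of code on an imputation already foreseen, with no new data. The article says data analysis has not begun, so this can still be prespecified. Downside: the delta range is a judgement, and a positive result may be reported as less certain.
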